##### 10-m walk test (10MWT)

During the 10MWT, participants walk 13 m in a straight line of which the last 10 m are timed using a stopwatch. The first 3 m are used to accelerate to the comfortable walking speed. When the first foot crosses the 3 m line the timer starts. When the first foot crosses the 13 m line the timer stops and participants are instructed to stop walking. Participants perform the test three times at a comfortable walking speed. The outcome measure is the mean time of these three performances [38].

##### Daily life walking

Daily life walking will be evaluated in terms of the amount of walking, and in terms of spatiotemporal gait parameters (e.g., stride time). For the amount of walking, participants will wear an Activ8 Physical Activity Monitor (Activ8, Remedy Distribution Ltd., Valkenswaard, The Netherlands) attached to one of the upper legs for seven consecutive days. Using customized algorithms the time spent in different activity classes (lying, sitting, standing, walking, running, cycling) will be determined based on the acceleration data collected by the activity monitor [39]. The outcome measure for this study is the mean time spent walking per day averaged over the total number of days the monitor is worn. For spatiotemporal gait parameters, participants will wear three inertial measurement units for 3 to 4 days: one on each foot and one on the lower back. Customized algorithms will be used to identify gait bouts, and derive the spatiotemporal parameters from these gait bouts. During these monitoring periods, participants are allowed to use all types of (orthopedic) walking aids, as they would normally use in daily life.

##### Activities-specific Balance Confidence scale (ABC scale)

The ABC scale is a questionnaire consisting of 16 items asking about how confident participants are to maintain their balance while performing different activities of daily life. Scores range from 0 to 100% confident [40].

##### Stroke Impact Scale–Mobility Subscale (SIS-mobility)

The SIS-mobility is a questionnaire evaluating disability and health-related quality of life after a stroke [41]. The Dutch Mobility subscale will be used in this study. Scores will be given on a 5-point scale, with higher scores indicating a lower impact of the stroke on daily life.

##### Fall reports

Each month, the participants are asked how many times they have experienced a fall in the preceding month through an online survey (CastorEDC) sent by email to the participants. A fall is defined as “an event which results in a person coming to rest inadvertently on the ground or other level” as defined by the World Health Organisation [42]. If one or two falls are reported, the participant is asked to report a short description of these events and the circumstances. In case the participant reports more than two falls, additional information is asked about the last two events.

### Data collection, management, and monitoring

Each participant receives a unique unidentifiable code generated by Castor EDC (www.castoredc.com). This code is assigned to the participant in order of inclusion of the subject. The identification code list is a protected file and is held separate from the data. This file is only accessible for researchers and administrative assistants working on the project. The collected data will be entered into Castor EDC. Handling of data will comply with the Dutch Personal Data Protection Act. After completion of the study, data will be stored for 15 years according to the Dutch national legislation. Researchers affiliated with the Sint Maartenskliniek and this study will have access to the data.

Monitoring and quality assurance will be established according to the NFU (Dutch Federation of University Medical Centres) guidelines for negligible risk intensity. Monitoring will be executed by an independent qualified monitor.

### Safety

The classification for risk is estimated at negligible risk. In case of an adverse event that is reported spontaneously by the subject or observed by the investigator or his staff, this will be recorded and reported to the accredited METC. All adverse events will be followed until they have abated, or until a stable situation has been reached. Depending on the event, follow-up may require additional tests or medical procedures as indicated, and/or referral to the general physician or a medical specialist.

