**Method:**

This is a single-center, randomized, waiting-list controlled trial. We aim to enroll 84 people in the chronic phase (> 6 months) after a first, unilateral supratentorial stroke, who are able to walk independently for 10 min. Following baseline assessment, participants will be randomly assigned to either the experimental group or the waiting-list control group. The experimental group will receive ten 1-h training sessions on the C-mill targeting walking adaptability in a 5-week period. Participants assigned to the waiting-list controlled group will continue their usual care for 5 weeks; thereafter they will receive the same walking adaptability training as the experimental group. To determine the effects of the training, assessments of walking adaptability, as well as other balance and gait-related tasks, will be conducted at baseline (T0) and following the 5-week intervention/waiting period (T1). To allow responder analysis across both groups, the waiting-list control group will have an additional assessment (T2) following their training period.

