**Fig. 1 Fig1:**
[figure not shown]
Timeline for the study

After conducting all the assessments during T0, participants are randomized to either the experimental group or the waiting-list control group. Participants will then either train or wait for 5 weeks, followed by a second assessment (T1) within 1 week after this period. Assessments at T1 are equal to baseline assessments (T0) in combination with the home-based monitoring period. Following T1, the waiting-list control group will receive the same walking adaptability training as the experimental group. They will undergo an additional assessment (T2) after the training period, identical to T0 and T1 assessments, to be used for responder analysis. Participants will also fill in a short questionnaire every month from baseline onward to report falls in the preceding month.

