**Fig. 2 Fig2:**
[figure not shown]
C-mill

The walking adaptability training program consists of ten 1-h sessions over a 5-week period. The training protocol is based on the previously published C-mill training protocol [20, 21], and further refined by our research team. Every training session will be guided by physical therapists with ample experience delivering C-mill training. Different physical therapists can guide the training sessions of one participant. Consistency of the content progression of the training between physical therapists is safeguarded by a protocol and logging of all training sessions.

Each training session consists of a set of exercises targeting the different components of walking adaptability: obstacle negotiation, target stepping, accelerating-decelerating, slalom walking and tandem walking. These components will be delivered separately, and in games combining multiple components. A total of eight different tasks (see Table 1) are included in the training protocol. Each task contains multiple levels of difficulty to enable progression between the training sessions (see Table 1). Progression of the training program is standardized for each task using success scores provided by the C-mill (see Appendix 1). The difficulty of the tasks can be varied through changes in walking (i.e., belt) speed and the addition of cognitive secondary tasks (i.e., dual tasking). The physical therapists are instructed to increase or decrease the difficulty level, based on the thresholds for the success scores defined by Timmermans et al. (2018) (see Table 2). If the proposed changes in difficulty are considered too challenging or too easy, the physical therapist is allowed to deviate, relying on their own clinical judgment. Training progression (including deviations) is logged by the therapist.

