#### Waiting-list control group

During the 5-week waiting period, participants continue their usual care. The standard of care for people in the chronic phase after a stroke in the Netherlands can for instance be physical therapy or occupational therapy, dependent on the situation of the individual participant. No additional therapy or program is provided during the waiting-list control period. The number of therapy sessions during the waiting period will be recorded at T1. Following T1, participants receive the same walking adaptability training program as the intervention group. In case participants regularly receive BTX, assessments are scheduled to minimize the influence of BTX on the measurements and no injections are scheduled during the walking adaptability training period: T0 will be scheduled 4 weeks pre-injections, T1 will be scheduled 4 weeks post-injections, and T2 will be scheduled 10 weeks post-injections [20].

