#### Criteria for discontinuing or modifying allocated interventions

Participants can leave the study at any time for any reason if they wish to do so, without consequence. The investigator can decide to withdraw a participant from the study for urgent medical reasons. In case a participant leaves the study before intervention allocation, the participant will be replaced, with a maximum of 10 replaced participants. Participants who leave the study after intervention allocation will not be replaced.

The intervention can be discontinued or modified due to the appearance of (serious) adverse events of a nature, severity and duration previously unknown, or of known (serious) adverse events occurring with an unexpectedly high frequency. However, given the absence of serious adverse events observed in the clinical practice with this type of training in this population, this is not expected.

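### Apart from falls, adverse events are recorded only if volunteered or observed, while staff contact up to T1 differs by design, so raw counts by arm would be open to ascertainment bias

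*Protocol article*

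**What the plan says.** **Capture rule.** The Safety section of the protocol article sets out when an event is recorded and reported to the ethics committee: "In case of an adverse event that is reported spontaneously by the subject or observed by the investigator or his staff". It describes no scheduled enquiry about adverse events.

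**Contact in the experimental arm.** Under Interventions, Experimental group: "The walking adaptability training program consists of ten 1-h sessions over a 5-week period". The same section adds: "Every training session will be guided by physical therapists with ample experience delivering C-mill training".

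**Contact in the waiting-list arm.** Under Waiting-list control group: "No additional therapy or program is provided during the waiting-list control period". The number of usual-care therapy sessions is recorded once, at T1. The same training follows after T1.

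**Falls.** These are handled differently. Participant timeline: "Participants will also fill in a short questionnaire every month from baseline onward to report falls in the preceding month". Fall reports repeats this, with an emailed survey and a definition that does not require injury: "Each month, the participants are asked how many times they have experienced a fall in the preceding month through an online survey". Neither section restricts the survey to one arm.

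**Use of event frequency.** The section on discontinuing or modifying the intervention names, as one ground, "known (serious) adverse events occurring with an unexpectedly high frequency". The next sentence refers to experience in clinical practice, not to the control arm.

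**The concern.** An event that must be volunteered or seen has a chance of being recorded only when the participant is in touch with someone who can record it. The two arms differ sharply in that respect during the only period in which they are a randomized comparison of training against no training. Pain, fatigue, strain or a visit to a doctor is likely to come up at one of ten supervised sessions. The same complaint in a control may have faded by T1 and never be mentioned.

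If adverse events are later tabulated by arm up to T1, as readers of a trial report will expect, an excess in the trained arm could not be separated into a true effect of training and a difference in opportunity to record. Events missed in the untrained arm cannot be reliably recovered afterwards. The later training of the waiting-list arm does not repair this, because a control's waiting phase and training phase differ in contact in the same way.

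**Working it through.** The article states no adverse-event rate, so there is no figure of the plan to reproduce. The check is a count of contacts, a comparison of the routes by which an event can be recorded, and an illustration under stated assumptions.

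**1. Scheduled face-to-face contacts from randomization to T1.** Randomization follows completion of T0 (Participant timeline).
- Experimental arm: 10 sessions + T1 = 11.
- Waiting-list arm: 0 sessions + T1 = 1.

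**2. Routes to a recorded event in that window.**

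| Route | Experimental | Waiting list |
|---|---|---|
| Observed by staff | 10 sessions and T1 | T1 |
| Volunteered face to face | 10 sessions and T1 | T1 |
| Volunteered through contact about appointments (Participant retention) | yes | yes |
| Solicited: falls, monthly | yes | yes |
| Solicited: other adverse events | none described | none described |

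Falls are asked about in the same way in both arms, regardless of clinic visits. For all other events the first two rows drive recording, and those rows are unequal.

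**3. Illustration of size.** Number per arm: 84 randomized at 1:1, so 84 / 2 = 42 (Sample size; Group allocation and blinding). The other inputs are assumptions with no source in the article: the same true risk of 20% in both arms, and 90% of events captured in the trained arm.

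True events per arm = 42 × 0.20 = 8.4. Recorded events = 8.4 × capture probability. Trained arm: 8.4 × 0.9 = 7.6.

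| Assumed capture, waiting list | Recorded, waiting list | Ratio, trained to waiting list |
|---|---|---|
| 0.9 | 7.6 | 0.9/0.9 = 1.0 |
| 0.7 | 5.9 | 0.9/0.7 = 1.29 |
| 0.5 | 4.2 | 0.9/0.5 = 1.8 |
| 0.3 | 2.5 | 0.9/0.3 = 3.0 |

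The ratio is simply the quotient of the two capture probabilities; the true risk cancels. The table shows how the mechanism works. It does not estimate the bias in this trial.

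**The case against.** Several points on the other side are sound.

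- **No comparison by arm is planned.** Adverse events are not among the primary or secondary outcomes, and Statistical methods describes no safety analysis by arm. A reader might infer that a planned randomized safety comparison is biased. The article contains no such comparison, so the point concerns any count by arm that may be made later.
- **The frequency rule does not use the control arm.** A reader might infer that the ground for modifying or stopping the intervention lacks a fair comparator, or could be triggered falsely by under-recording in controls. The text sets frequency against expectation, with clinical practice as the only benchmark beside it. That inference is not supported.
- **Falls are covered.** A reader might infer that non-injurious falls in controls go unrecorded. The monthly survey solicits them in both arms. The article does not say that these reports are entered as adverse events, but they are recorded.
- **Controls have other contact.** Participant retention describes direct contact with research staff throughout. This stands as a route for volunteering events, but its stated purpose is appointments, and no health enquiry is described. It narrows the gap without closing it.
- **Detail may lie elsewhere.** The schedule in Table 3 is not shown in the text at hand, and a full protocol may hold an adverse-event form. This stands as a caution: a question at visits may exist. The point rests on the capture rule that the Safety section does state.
- **Risk is classified as negligible.** This argues against giving the matter high priority. It does not make unequal capture equal.

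Extra recorded events in the trained arm could also be real effects of training. That possibility is why the two explanations need to be separable.

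**Conclusion.** The point holds in limited form. Outside falls, the stated capture rule depends on contact, and scheduled face-to-face contact up to T1 is 11 against 1. Raw non-fall adverse-event counts by arm over that window would be open to ascertainment bias, probably towards more recorded events in the trained arm. The direction rests on the assumption that more contact gives more opportunity to volunteer or observe an event. The size cannot be derived from the article; under the assumptions shown, the ratio runs from 1.0 (equal capture) to 3.0. No estimate, sample size or error rate for the efficacy outcomes is affected. This is an inexpensive improvement to safety recording, not a flaw in the trial's main inference.

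**What to change.** In the Safety section, keep recording of volunteered and observed events and add:

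1. The same adverse-event question to both arms at T1, and to the waiting-list arm again at T2, covering any new health problem, injury or medical contact since the last enquiry.
2. The same question in the monthly Castor survey that already asks both arms about falls.
3. A flag on each event: solicited, or observed during a training session.
4. A statement that any summary by arm up to T1 uses the solicited events, with session-observed events listed separately.

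If the full protocol already holds such a question, it is enough to say so in the Safety section and to add items 3 and 4.

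The cost is one question at existing visits and in an existing survey, plus somewhat more minor events to record and to report to the ethics committee. One limit remains: participants know their allocation, so a common question equalizes the opportunity to report but not necessarily the readiness to do so.

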### Sample size

The sample size calculation was based on previous work comparing pre- to post-walking adaptability training intervention in a stroke population using the EFAP-obstacle (effect size: 0.7) [8]. Assuming a change of 10% of the intervention effect size in the waiting list control group, each group should include 47 participants to achieve a power of 80%, setting the alpha level at 0.025 to correct for two primary outcome measures. A correction factor was applied to account for a correlation (*r* = 0.5) between T0 and T1 [43], resulting in 35 participants per group. Taking 15% attrition into account, in total 84 participants will be randomized.

### Statistical methods

To evaluate the effect of the training program, an intention-to-treat analysis will be conducted as the primary analysis. All participants who are randomized to one of the two study arms (including those who drop out during the intervention period, or never started the intervention) will be included in the primary analysis. In addition, a per-protocol analysis will be performed, excluding participants in the experimental group not completing the training program or participants in the waiting-list control group receiving training targeting walking adaptability. The training program is considered complete if at least 8 out of 10 training sessions are concluded.

The effect of the walking adaptability training on primary and secondary outcomes will be tested with a linear mixed model. The scores at post-intervention (T1) will be used as the dependent variable and group allocation (intervention or waiting-list control) as the independent variable; covariates are baseline scores of the dependent variable (T0) and the stratification variable (MI score), and participant ID as a random factor. A Bonferroni correction will be applied due to the two primary outcome measures; therefore significant effects are assumed for *p* < 0.025. Effects will be presented as the mean difference with 95% confidence intervals.

For the responder analysis, we will use the data of all participants who completed the training program in the study, because all participants underwent the walking adaptability training either as the experimental group or directly following the waiting-list period. To identify baseline participant characteristics that predict a response to training (defined as scores on the EFAP-obstacle or WALT), a linear regression model will be used. Predictors for response to the training will be collected during the intake assessment and T0 for both groups. To determine response to training, the relative change in EFAP-obstacle and WALT at T1 for the experimental group and T2 for the waiting-list control group will be used. Age, Motricity Index score and the miniBESTest score will be tested for their predictive value, and an exploratory analysis will be performed on other variables that may predict outcome.

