### Outcomes

For all outcomes, the primary endpoint of this trial is the measurement at T1. The reported statistics will include mean group differences and the associated 95% confidence intervals, as well as group means with SD.

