#### Primary outcomes

We include two primary outcome measures for evaluating walking adaptability, the obstacle avoidance subtask of the Emory functional ambulation profile (EFAP-obstacle) and the walking adaptability ladder test (WALT) [29, 30]. The EFAP-obstacle has previously been used as an outcome measure for walking adaptability in a stroke population [8], but is expected to show a ceiling effect in our research population of community ambulators [31]. Therefore, we additionally used the newly developed WALT, which has been shown to be responsive to walking adaptability training effects in adults with hereditary spastic paraplegia and in children with developmental disorders [32, 33], but has not yet been validated in PwS.

During the EFAP-obstacle, participants traverse a standardized 5 m obstacle course at a comfortable walking speed, including stepping over two boxes (10(l) × 100(w) × 5(h) cm) put on the floor, and turning around a chair without touching it. Time to complete the EFAP-obstacle task is the main outcome parameter.

The WALT consists of a 10 m agility ladder with 18 stepping targets, which progressively decrease in length (2 cm per target, ranging from 69 to 35 cm). Participants are instructed to walk back and forth over the ladder as fast and accurately as possible, in single and double run conditions. During the single run, one foot is placed in each target. During the double run, both feet are consecutively placed in each target. Accuracy is rated by counting the number of stepping errors (wrong number of feet per target, touching the borders of the target or jumping in double run). Each error results in a 1-s time penalty. Execution of the WALT is recorded by video, following the recommendation of Kuijpers et al. (2020) to ensure reliability [30]. The video recordings are used to identify errors, and to record the time needed to complete the WALT. The main outcome measure is the sum of the time needed to complete the WALT plus the time penalty.

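### The primary mixed model has one T1 score per participant, so its participant random factor is redundant and should be dropped in favour of ANCOVA

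*Protocol article*

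**What the plan says.** The Statistical methods section gives one model sentence for every outcome: "The effect of the walking adaptability training on primary and secondary outcomes will be tested with a linear mixed model". It then defines the two sides of the model. On the left, "The scores at post-intervention (T1) will be used as the dependent variable". On the right are group allocation and the following terms: "covariates are baseline scores of the dependent variable (T0) and the stratification variable (MI score), and participant ID as a random factor".

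Three other places fix how many rows a participant contributes to the primary model:
- Outcomes: "For all outcomes, the primary endpoint of this trial is the measurement at T1".
- Primary outcomes, EFAP-obstacle: "Time to complete the EFAP-obstacle task is the main outcome parameter".
- Primary outcomes, WALT: "The main outcome measure is the sum of the time needed to complete the WALT plus the time penalty".

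The Participant timeline section describes the T2 assessment, made only in the waiting-list group, as "identical to T0 and T1 assessments, to be used for responder analysis". T2 therefore adds no rows to the primary comparison.

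**The concern.** A random effect for participant is informative only when participants contribute more than one row. Here T0 is a covariate and T1 is the sole response, so each participant has one row per primary outcome. The participant effect and the residual are then the same quantity under two names. The sentence appears to merge two sound models: ANCOVA on T1, and a repeated-measures mixed model with T0 and T1 both as responses.

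This is the only stated confirmatory analysis of both primary outcomes, and it is tested at a deliberately reduced alpha of 0.025. An analyst who fits it as written may meet a refusal to fit, a convergence or singular-Hessian warning, or standard errors that look usable but are wrong.

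**Working it through.** **Inputs.** From Sample size: effect size 0.7, reduced by 10% for change in controls; alpha 0.025; power 80%; T0–T1 correlation r = 0.5; 47 per group before and 35 after the correlation factor; 15% attrition; 84 in total. From Group allocation and blinding: 1:1 allocation. Sidedness is not stated; two-sided is assumed because it fits the stated figures (one-sided gives 40 per group).

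**Step 1: reproduce the plan's sample size.**
- Effect: 0.7 × 0.9 = 0.63.
- n per group = 2 × (2.2414 + 0.8416)² / 0.63² = 47.9, rounded up to 48, against 47 stated.
- Correlation factor: 1 − 0.5² = 0.75, and 47 × 0.75 = 35.25, about 35 as stated.
- Attrition: 35 / 0.85 = 41.2, rounded up to 42 per group, or 84 in total as stated.

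The factor 1 − r² is the variance reduction from ANCOVA with the baseline score as covariate. The trial was therefore sized for ANCOVA.

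**Step 2: what the stated model implies.** With one row per participant, the covariance matrix of the responses is

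V = (participant variance + residual variance) × I.

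Only the sum appears, so only the sum can be estimated. The generalised least-squares estimate of the group effect under this V is the ordinary least-squares estimate, and its model-based standard error is the ANCOVA standard error.

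**Step 3: numerical check on one simulated data set** (70 participants, r = 0.5, effect 0.63 SD, one T1 row each). The total variance was held at the ANCOVA residual mean square of 0.658 and the participant share was varied:

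| Participant share of variance | REML log-likelihood (without constant) | Group effect | SE |
|---|---|---|---|
| 0% | −26.0506 | −0.5995 | 0.1949 |
| 50% | −26.0506 | −0.5995 | 0.1949 |
| 99% | −26.0506 | −0.5995 | 0.1949 |

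Shares of 10, 25, 75 and 90% gave the same values. ANCOVA gave −0.5995 with SE 0.1949.

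**Step 4: a literal fit of the same data.** The statsmodels MixedLM routine saw 70 groups of size 1 and warned that the Hessian was not positive definite. It split the variance arbitrarily as 0.329 and 0.329; the sum, 0.658, is correct. The group coefficient matched ANCOVA, but the reported SE was 0.174, which is 0.174 / 0.195 = 89% of the correct value.

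**Step 5: how far this can mislead.** In 1,200 null simulations at the planned size:
- 97% of the literal fits raised a warning.
- Standard errors ran from 10% to 100% of the ANCOVA value.
- Rejection at p < 0.025 was 4.6%, against 1.75% for ANCOVA. Monte Carlo standard errors are √(0.046 × 0.954 / 1200) = 0.6 points and √(0.0175 × 0.9825 / 1200) = 0.4 points.

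Two smaller sets, of 400 and 300 null data sets, gave 7.8% and about 7%. The inflation is real for that routine, but its size is only roughly fixed.

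**Step 6: effect of the repair on power.** For ANCOVA with 35 per group, the standardised effect is 0.63 / (√0.75 × √(2/35)) = 3.043. Normal-approximation power is Φ(3.043 − 2.241) = 78.9%, close to the stated 80%. The sample size does not need to change.

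**The case against.** The best defence is that no reported result uses the variance split. The confirmatory quantity is the adjusted mean difference with its confidence interval, and in theory both equal those from ANCOVA. This stands, and it rules out three stronger readings that a reader might infer:

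- **That the model makes the effect biased or inestimable.** It does not. Only the split is unidentified; the coefficient agrees with ANCOVA to rounding error.
- **That the plan carries a fixed type I error of 0.0284.** That figure comes from using the normal critical value 2.2414 with 66 degrees of freedom (70 − 4): 2 × P(t > 2.2414) = 0.0284. The arithmetic is right, but it assumes z-based tests. The article names no z test, no software and no degrees-of-freedom method, and such detail is commonly left to an analysis plan.
- **That the analyst would be forced to choose a new primary model after seeing the data.** Deleting the redundant term leaves group, T0 and Motricity Index, all already named, with the same estimate and the same theoretical standard error. It can be done before any data are analysed.

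Two further objections carry some weight. First, the sentence is generic and also covers secondary outcomes. Some of these come from repeated measurements, such as the inward and outward perturbations in the gait stability test, where a participant effect can be meaningful. Second, one row per participant is the natural reading of the primary outcomes but not an explicit statement: the number of EFAP-obstacle trials is not given, and the text does not say in so many words that the WALT single and double runs are added together. Analysing those runs as separate rows would sit badly with a single summed WALT score and would not help EFAP-obstacle.

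It is also fair to say that the small standard errors are an artefact of one routine working with a singular Hessian, and that it nearly always warned. That limits how far the simulated error rates generalise. It does not make the model sentence correct.

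**Conclusion.** The point holds as a mis-specified sentence in the primary analysis. For EFAP-obstacle and WALT the participant random factor is redundant and its variance cannot be separated from the residual. Properly handled, the treatment estimate and its standard error are those of ANCOVA, so the trial's question can still be answered.

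The practical harm comes from a literal fit: warnings or non-convergence and, in at least one common package, standard errors that are too small, with rejection of roughly 5% to 8% in null data at a nominal 2.5%. That range comes from one routine at the planned size and should not be quoted as the trial's error rate. The conclusion rests on one score per participant per primary outcome at T1, which is how the article defines both outcomes.

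**What to change.** In Statistical methods, for outcomes with one score per participant, delete the participant random factor and state the primary model as ANCOVA: T1 score on group, T0 score and Motricity Index, with t-based tests and confidence intervals. Keep a participant random effect only for outcomes analysed with several rows per participant, and say what the rows are.

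A longitudinal mixed model with T0 and T1 both as responses, including time and group-by-time terms, is an acceptable alternative. It would let participants with T0 but no T1 contribute, but it is a different model and is not needed to cure this defect. If the sponsor prefers it, it should be named before the data are analysed.

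The cost is one phrase in the protocol or analysis plan. Data collection, sample size and trial conduct do not change.
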